## Abstract

**Background:**

Gestational diabetes mellitus (GDM) is defined as glucose intolerance with its onset or first recognition during pregnancy. Post-GDM women have a life-time risk exceeding 70% of developing type 2 diabetes mellitus (T2DM). Lifestyle modifications reduce the incidence of T2DM by up to 58% for high-risk individuals.

**Methods/Design:**

The Mothers After Gestational Diabetes in Australia Diabetes Prevention Program (MAGDA-DPP) is a randomized controlled trial aiming to assess the effectiveness of a structured diabetes prevention intervention for post-GDM women. This trial has an intervention group participating in a diabetes prevention program (DPP), and a control group receiving usual care from their general practitioners during the same time period. The 12-month intervention comprises an individual session followed by five group sessions at two-week intervals, and two follow-up telephone calls. A total of 574 women will be recruited, with 287 in each arm. The women will undergo blood tests, anthropometric measurements, and self-reported health status, diet, physical activity, quality of life, depression, risk perception and healthcare service usage, at baseline and 12 months. At completion, primary outcome (changes in diabetes risk) and secondary outcome (changes in psychosocial and quality of life measurements and in cardiovascular disease risk factors) will be assessed in both groups.

**Discussion:**

This study aims to show whether MAGDA-DPP leads to a reduction in diabetes risk for post-GDM women. The characteristics that predict intervention completion and improvement in clinical and behavioral measures will be useful for further development of DPPs for this population.

**Trial registration:**

Australian New Zealand Clinical Trials Registry ANZCTRN 12610000338066

## Background

Type 2 diabetes (T2DM) and gestational diabetes mellitus (GDM) are escalating problems worldwide. Depending on the population studied, 1 to 14% of all pregnancies are complicated by GDM [1]. This estimate may double if the International Diabetes Association of Diabetes and Pregnancy Study Groups (IDAPSG) recommended criteria are implemented [2].

Gestational diabetes mellitus is defined as glucose intolerance of variable severity with onset or first recognition during pregnancy [3]. Post-GDM women have a life-time risk of developing T2DM exceeding 70% [4]. In Australia, between 2005 and 2006, GDM was diagnosed in 4.6% of hospital births, and the incidence increased by 22% over 6 years from 3.6 per 100 pregnancy in 2000/01 to 4.4 per 100 pregnancy in 2005/06 [5]. Risk factors for GDM include family history of diabetes, age over 30 years, overweight or obesity at time of conception, and belonging to a high-risk ethnic group (for example, Aboriginal and Torres Strait Islander, Pacific Islander, South Asian, Middle Eastern) [6,7].

Pregnancies complicated by GDM have increased incidence of fetal macrosomia. This in turn leads to an increased risk of caesarean deliveries, maternal pre-eclampsia, and neonatal complications including hypoglycemia, shoulder dystocia, and birth trauma [7]. Women with GDM also have a significantly increased risk (by approximately 25% of absolute risk) of developing T2DM within 15 years relative to women without GDM [8] and a 30 to 69% increased risk of developing GDM in subsequent pregnancies [9]. GDM also puts the child at risk, with the offspring of mothers with GDM having an increased risk of obesity and abnormal glucose metabolism during childhood, adolescence, and adulthood [10].

In Australia, the prevalence of T2DM has more than doubled since 1981, with 3.8% of Australians, almost one million, having been diagnosed with T2DM in 2007 to 2008 [11]. It is also estimated that at least half of those who have T2DM are undiagnosed, and so are unaware of their condition [12]. Currently, diagnosed diabetes is the second highest contributor to the Australian burden of disease, responsible for 5.2% of disability adjusted life-years. It is estimated that by 2023, T2DM will be the leading contributor, responsible for 8.6% of overall disease burden [13], resulting from the major morbidity of diabetes complications. Diabetes also poses an enormous economic burden, accounting for A$1.4 billion (or US$ 1.26 billion, approximate exchange rate A$1 to US$0.9) in healthcare expenditure in 2003, which is projected to increase to almost A$7 billion (US$6.3 billion) by 2033 [14].

Therefore, there is an urgent need to implement a widespread and coordinated approach to prevent T2DM. Several clinical trials have shown that lifestyle modification with weight loss and moderate exercise can reduce the incidence of T2DM by up to 58% for people at high risk [15-17]. Indeed, these lifestyle modification programs have been shown to be even more effective than drug treatment in clinical trials [7,16,18], and have a lasting effect that is still evident eight years from the onset of intervention and four years after the active intervention has ceased. The diabetes prevention program conducted in the United States (US DPP) included 350 women with previous GDM [7]. The results showed a greater conversion to diabetes for GDM than non-GDM women; however, both groups responded to metformin treatment and lifestyle interventions [7].

One way to approach this problem is target individuals at high risk of developing diabetes. Previous studies such as the US DPP and the Finnish prevention study [19] have targeted individuals with glucose dysregulation as identified by an oral glucose tolerance test. A history of GDM is one of the major risk factors in women who should be targeted for preventing development of T2DM.

### Mothers After Gestational Diabetes in Australia study

The Mothers After Gestational Diabetes in Australia (MAGDA) aims to develop and implement a macro-level system change to reduce the risk of progression to T2DM for women with previous GDM. The project consists of four components: (1) a register to facilitate appropriate follow-up after diagnosis of GDM; (2) an intervention to reduce progression to T2DM; (3) a health economics evaluation of the register and intervention; and (4) an understanding of how to implement the register and follow-up in general practice. This paper presents the protocol for the intervention, a randomized controlled trial (RCT) of the Mothers After Gestational Diabetes in Australia Diabetes Prevention Program (MAGDA-DPP). The MAGDA-DPP trial offers an evidence-based structured lifestyle modification group-based intervention for women who have had GDM. The objectives of MAGDA-DPP are that the intervention will result in favorable changes, relative to usual care, in clinical, behavioral and patient-relevant outcome. In addition, MAGDA-DPP aims to identify individual characteristics predictive of successful outcome.

## Methods/Design

### Study design

MAGDA-DPP is a prospective, open RCT to assess the effectiveness of a structured diabetes prevention program (DPP) for women who have had GDM. This trial has an intervention group participating in a DPP and a control group receiving usual care from their general practitioners (GPs) during the same time period. Women will be recruited from two Australian State capital cities, Melbourne and Adelaide.

All women recruited into the study will be followed up for 12 months. At baseline, the women will undergo an assessment consisting of blood tests, anthropometric measurements, and self-reported assessment of health status, diet, physical activity, quality of life, depression and risk perception. The intervention group will be assessed at baseline, and at three and 12 months. The control group will be assessed at baseline and 12 months.

The MAGDA-DPP intervention is coordinated by Deakin University (Melbourne Campus) and is supported by a ‘Partnerships for Better Health’ Grant from the National Health and Medical Research Council of Australia (NHMRC). The project includes multiple study partners, consisting of two state governments, three universities and two non-government organizations. Study partners, recruiting hospitals and relevant ethics approvals are listed in Table 1.

**Table 1 T1:** MAGDA project study partners, recruitment sites and relevant ethics approvals

**Study partner/recruitment site (state)**	**Ethics approval authorities (reference number)**
Deakin University (VIC)	Deakin University human research ethics committee (2010–005)^1^
Flinders University (SA)	Southern Adelaide Clinical Network human research ethics committee (330/10)
The University of Melbourne (VIC)	NA
Department of Health (VIC)	NA
South Australia Health (SA)	South Australia Health human research ethics committee (339/02/2013)
Diabetes Australia Victoria branch (VIC)/NDSS	Deakin University human research ethics committee (2010–005)^1^
GP-Victoria	NA
The Royal Women’s Hospital (Vic)	The Royal Women’s Hospital (10/06)
Sunshine Hospital (VIC)	Melbourne Health (2010.008)
Lyell McEwin Hospital (SA)	The Queen Elizabeth Hospital/Lyell McEwin Hospital HREC (2011109)^2^; South Australia Health human research ethics committee (339/02/2013); South Australia Aboriginal Health research ethics committee (04-10-331)

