#### Primary outcome

The primary outcome is the change in diabetes risk, as determined by changes in FPG, weight, or waist circumference. A statistically significant change in any one of these three endpoints will be regarded as evidence of a change in diabetes risk. No adjustments to significance levels will be made for multiple testing. These co-primary outcome will be assessed at baseline and 12 months for all women, and additionally at 3 months (or as soon as possible after the final group session) for the intervention participants only.

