### Anthropometric measurements and laboratory testing

To ensure that the clinical measurements meet research standards, measurements will be carried out by specially trained study nurses/phlebotomist. All clinical tests will follow the latest international recommendations from the European Health Risk Monitoring protocol [27]. Blood samples will be collected by the study nurse/phlebotomist, and analyzed by Melbourne Pathology (Victoria) or ClinPath (South Australia). Anthropometric measurements including height, weight, waist and hip circumference, and blood pressure will be taken. Women will be asked to fast from 10 pm the night before their appointment and venous samples will be drawn at the appointment to analyze lipids (triglycerides, total cholesterol, low-density lipoprotein and high-density lipoprotein cholesterol), HbA1c and glucose (fasting and 2 hour OGTT). Additional blood from women who consent to having their blood stored will be bio-banked at −80°C for further additional analyses.

For the intervention group only, at three months after baseline testing or as soon as possible after the final group session, a follow-up assessment will repeat all blood tests (except OGTT), and anthropometric measurements of weight and waist circumference. All women who complete this clinical testing will receive a standardized feedback letter documenting their results and any evidence of high blood pressure or depression. A copy will be sent to their nominated GP.

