### Data collection

Participants’ blood test results will be uploaded onto the Melbourne Pathology/ClinPath websites, which are password-encrypted. In order to protect confidentiality, the participant ID number and date of birth will be the only identifying information available to the laboratory. Melbourne Pathology will also post hard copies of the pathology results to the study office (Deakin University), and ClinPath will send their hard copy results to the study office in South Australia in secure envelopes via ClinPath couriers.

Web-based survey forms will be used primarily to collect information during the testing appointment, with the paper-based system used as a back-up. Clinical measurements will be recorded by the study nurse. All questionnaires are self-reported by the participating women, and will use the participant ID number (on the front of each form/questionnaire) as the identifier. Only the demographic questionnaire contains the participants’ contact details, and this will be maintained separately from all of the other information relating to each woman.

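### Nothing in the open design masks the nurses who take 12-month waist and weight, an intervention-only 3-month visit reveals the arm to whoever does it, and either measure alone can carry the primary conclusion

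*Protocol article*

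**What the plan says.** Under Study design, the protocol article describes the trial without qualification as open: "MAGDA-DPP is a prospective, open RCT to assess the effectiveness of a structured diabetes prevention program (DPP".

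Under Primary outcome, three endpoints are named: "The primary outcome is the change in diabetes risk, as determined by changes in FPG, weight, or waist circumference". Success on one is enough: "A statistically significant change in any one of these three endpoints will be regarded as evidence of a change in diabetes risk". Each is tested at the full level: "No adjustments to significance levels will be made for multiple testing".

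Anthropometric measurements and laboratory testing says that "measurements will be carried out by specially trained study nurses/phlebotomist", and Data collection adds "Clinical measurements will be recorded by the study nurse".

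The same measurement section sets an additional assessment: "For the intervention group only, at three months after baseline testing or as soon as possible after the final group session". It repeats the blood tests apart from the OGTT and takes "anthropometric measurements of weight and waist circumference". Study design confirms that control women are assessed only at baseline and 12 months.

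Under Randomization, allocation follows receipt of the baseline blood results, and the assignment is displayed to the user in the randomization office. The woman and her GP are told by letter. No section says whether the nurses who measure at 12 months are kept unaware of the arm.

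**The concern.** A waist reading depends on where the tape is placed and how tightly it is drawn. An assessor who knows the arm can shift it without intending to. Scale weight is less exposed, and laboratory FPG least.

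Three stated features combine. The trial is open, with no exception for assessors. The 3-month visit exists for one arm only, so attending it reveals the arm to whoever measures. The success rule lets waist or weight carry the conclusion alone, so an unaffected FPG result does not protect it.

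Baseline does not cancel such an error. Baseline values are obtained before randomization, so knowledge of the arm cannot affect them. A differential error at 12 months passes straight into the change from baseline. At stake is a primary conclusion of reduced diabetes risk that rests on how a tape was held.

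**Working it through.** **Inputs from the article** (Sample size and power calculation): two-sided 5% level, 80% power, effect size 0.27, 215 per arm evaluable, 25% attrition, 287 per arm recruited.

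**Reproducing the plan's figure.** n per arm = 2(1.960 + 0.842)² / 0.27² ≈ 215.3, against 215 stated; rounding up gives 216. Allowing for attrition, 215 / 0.75 = 286.7, so 287 per arm and 574 in total, as stated. The evaluable 215 per arm is used below.

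**Inputs that are assumptions.** The article gives neither an SD for 12-month waist change nor any size of measurement bias. I take an SD of 5 to 8 cm and an average bias b of 0.5 or 1 cm across the whole intervention arm, with no true effect on waist.

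**Formula.** Shift of the test statistic: ncp = (b / SD) × √(215 / 2) = (b / SD) × 10.37. Two-sided rejection rate: 1 − Φ(1.96 − ncp) + Φ(−1.96 − ncp).

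| Arm-level bias | SD 5 cm | SD 6 cm | SD 8 cm |
|---|---|---|---|
| 0 | 5.0% | 5.0% | 5.0% |
| 0.5 cm | ncp 1.037, 17.9% | ncp 0.864, 13.9% | ncp 0.648, 9.9% |
| 1 cm | ncp 2.074, 54.5% | ncp 1.728, 40.8% | ncp 1.296, 25.4% |

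**Partial exposure.** If only a fraction f of intervention women are measured at 12 months by a nurse who knows their arm, the arm-level bias is f × b. With f = 0.5 (an assumption), a 1 cm error per exposed woman becomes 0.5 cm for the arm, and the 1 cm row falls to the 0.5 cm row. At an SD of 6 cm that is 13.9% in place of 40.8%.

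**Effect on the any-one-of-three rule.** With independent endpoints and no bias, the chance of at least one false positive is 1 − 0.95³ = 14.3%. That part is a multiplicity matter and is not charged to this point. With a bias in waist only of 0.10 SD (0.5 cm at SD 5 cm) it is 1 − 0.95² × (1 − 0.179) = 25.9%. With 0.20 SD it is 59.0%. Assuming correlations of 0.7 between weight and waist and 0.2 with FPG, simulation gives 12.7% without bias, then 24.5% and 59.0%. The increment due to waist bias is much the same either way.

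No figure is given for weight; the documents offer no basis for one.

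**The case against.** The strongest objection is that silence is being read as fact. A group lifestyle programme cannot be masked to participants or facilitators, so calling the trial open does not settle whether the 12-month assessors are masked. The article is condensed, and a full protocol that is not shown may mask them. This stands as a limit: the article can be faulted only for what it fixes. But it does fix an arm-revealing measurement visit and a rule that lets waist or weight suffice. Those are stated design choices, not details left to another document.

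A reader might infer that the nurses know the allocation, or that the nurse at 12 months is the one who saw the woman at 3 months. The documents support neither. They refer to nurses in the plural, across two states, and do not say who measures whom. Randomization places the assignment in the randomization office and gives no sign that nurses can see it. What follows from the text is narrower: whoever does the 3-month visit learns the arm.

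The article also provides for specially trained staff and for clinical tests that follow an international measurement protocol. That limits how large a bias is plausible and reduces random error. It does not stop technique drifting with knowledge of the arm.

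Finally, the error rates rest on assumed SDs and an assumed arm-wide bias. That is right, and they should be read only as illustration.

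**Conclusion.** The concern holds in limited form. As written, the schedule and success rule expose waist, and to a lesser degree weight, to differential measurement at 12 months, and nothing in the article guards against it. Neither the pre-randomization baseline nor standardized technique removes the risk.

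The result depends on three assumptions: an SD of waist change of 5 to 8 cm, a bias averaged over the whole intervention arm, and 215 evaluable women per arm. It would be tempting to take 41% (1 cm, SD 6 cm) as the trial's error rate. The documents do not support that: they report no bias, and exposure may be partial. If the full protocol already masks the 12-month assessors, one sentence in the article settles the point. This is something the sponsor should correct; it is not a demonstrated bias.

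**What to change.** State in the measurement section that 12-month waist and weight are taken by a nurse who has not been told the allocation. Keep the assignment within the randomization office as far as the measuring nurses are concerned. Ask women not to disclose their group at the visit. Where existing staffing allows, have a nurse other than the one who did the 3-month visit take the 12-month measurement. Record whether the nurse became aware of the arm, and use that record in a sensitivity analysis, which the article already foresees in general terms.

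The endpoints, sample size and intervention stay as they are. The cost is some scheduling friction, a short request to the women and one extra item on the visit form. The article gives no nurse numbers, so how far rostering can separate the two visits is unknown, and masking will be imperfect because women may still reveal their group.

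Timing is favourable. Trial status reports that baseline testing began in July 2012 and gives its counts as of June 4, 2013, so on that date no 12-month measurement was yet due. Some 3-month visits had probably taken place, since six groups had been initiated. For those women the sponsor would need to check who did the visit.

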### Selection of participants

The inclusion criterion for women is diagnosis of GDM in their most recent pregnancy, with GDM defined by the Australasian Diabetes in Pregnancy Society (ADIPS) criteria: fasting plasma glucose (FPG) of 5.5 mmol/L or higher, and/or 2 hour glucose of 8.0 mmol/L or higher on a 75 g oral glucose tolerance test (OGTT) [3], or a glucose challenge test (GCT) result of 12.0 mmol/L or higher.

The exclusion criteria are: (1) pre-existing diabetes (Type 1 or 2 diabetes mellitus); (2) cancer (not in remission); (3) severe mental illness; (4) substance abuse (illicit drugs); (5) myocardial infarction in the preceding three months; (6) difficulty with English; (7) involvement in another post-natal intervention trial; and (8) pregnancy at post-natal baseline testing or at any point during the 12 months of study involvement.

Once women diagnosed with GDM express interest in the study, the recruiter (the MAGDA-DPP project manager or research assistant) will conduct the first eligibility screening, generally prior to the women delivering their babies. A subsequent post-natal screening will be conducted at time of baseline OGTT, to exclude women who have diabetes at that stage.

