### Randomization

Block randomization will be implemented and separate randomization lists for each ‘venue’ or ‘stratum’ will be created. Each list will be supplied as a separate file and will be imported into the current MAGDA management database, which selects the next available sequence number for the venue/stratum. This sequence number will be displayed, along with the assignment code (control or intervention) to the user in the randomization office at Deakin University.

Women will be randomized into either the intervention or control arm after the baseline blood results have been received by the MAGDA-DPP project manager. If the woman does not have diabetes, the project manager or senior program manager will randomize her using the MAGDA-DPP management database. Each woman will receive a letter with the outcome of her randomization along with her baseline test results, and a copy will be sent to her nominated GP.

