### Outcome assessment

At baseline and completion of the study (12 months after baseline), primary (changes in diabetes risk) and secondary (changes in cardiovascular disease risk factors, psychosocial and quality of life measurements) outcome will be assessed.

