### Sample size and power calculation

For the estimation of sample size for two groups, using a two-sided 5% significance level and 80% power, the total number required will be 430 (215 in each arm). The sample size calculation was based on the observed mean change in FPG over 12 months in the Greater Green Triangle Diabetes Prevention Program (GGT DPP) study [36] and is powered to detect an effect size of 0.27 (assuming mean difference between intervention and control groups of 0.14 mmol/L and within group standard deviation of 0.5 mmol/L). To allow for an estimated attrition rate of up to 25% (estimate based on the GGT DPP), we will require a total sample of 574 (287 in each arm). This sample size will provide sufficient power to also analyze changes in weight and waist circumference. The intention-to-treat (ITT) principle will be adhered to, and sensitivity analysis will also be carried out.

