### Data analysis

Analyses will be performed using STATA version 12 or later (Stata Corp., College Station, TX, USA) and the ITT principle will be adhered to. Baseline characteristics will be compared between the intervention and control groups using χ^2^ tests, independent t-tests, and/or the Wilcoxon rank-sum test, as appropriate. Primary and secondary outcome (as described above) will be evaluated using mixed models, treating ‘group’ as a between-subject factor, and ‘time’ as a within-subject factor. Two-sided tests will be used, with a level of *P*<0.05 determining statistical significance.

A separate and parallel economic evaluation protocol will be described elsewhere.

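### The pregnancy exclusion extends past randomisation and, on its natural reading, conflicts with the stated intention-to-treat analysis

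*Protocol article*

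**What the plan says.** Under Selection of participants, the final exclusion criterion is "8) pregnancy at post-natal baseline testing or at any point during the 12 months of study involvement". It therefore has two parts: pregnancy at entry, and pregnancy later in the study year.

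Under Randomization: "Women will be randomized into either the intervention or control arm after the baseline blood results have been received by the MAGDA-DPP project manager". The Consent section gives the same order: women found to have diabetes on the baseline bloods are excluded, and the rest are then randomised. Under Outcome assessment, the primary and secondary outcomes are measured "At baseline and completion of the study (12 months after baseline".

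Three other statements bear on who is followed and analysed:

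- Study design: "All women recruited into the study will be followed up for 12 months".
- Sample size and power calculation: "The intention-to-treat (ITT) principle will be adhered to, and sensitivity analysis will also be carried out".
- Data analysis: "the ITT principle will be adhered to", with mixed models using group and time as factors.

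The recruitment target rests on this allowance: "To allow for an estimated attrition rate of up to 25% (estimate based on the GGT DPP").

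**The concern.** An eligibility criterion should be checkable before allocation. The second part of this one is not, because almost all of the study year follows randomisation. If it is applied as an exclusion, the groups compared at 12 months are selected on something that happened after allocation, and the protection given by randomisation is weakened.

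The event is foreseeable, since participants enter from about three months after giving birth. All three co-primary endpoints (FPG, weight and waist circumference) are affected, because the same women would be missing from each.

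The trial is described as open ("MAGDA-DPP is a prospective, open RCT"), and contact differs by arm. The intervention group has six sessions, an assessment at about three months and two telephone calls. The control group has no scheduled study assessment between baseline and 12 months. Pregnancy, or the chance that it becomes known to the study, could therefore differ between arms. A secondary question is whether the sample-size allowance covers these losses.

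**Working it through.** **1. The passages side by side.** Randomisation follows the baseline results, and the study ends 12 months after baseline. A pregnancy that starts during study involvement is thus, with rare exceptions between baseline testing and allocation, a post-randomisation event. ITT keeps all randomised women in their allocated arm, and Study design promises 12 months of follow-up for all recruited women. An exclusion for a later pregnancy fits neither statement unless it is limited to something other than follow-up and analysis, and the article states no such limit.

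**2. The plan's own sample size.** Inputs from Sample size and power calculation: two-sided 5%, 80% power, effect size d = 0.27, 25% attrition.

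- Per arm: n = 2 × ((1.960 + 0.842) / 0.27)² = 215.3. The article states 215.
- Attrition: 215 / 0.75 = 286.7, so 287 per arm and 574 in total, as stated.
- Power at 215 per arm: Φ(0.27 × √(215/2) − 1.960) = Φ(0.839) = 79.9%.

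The target reproduces, and it has no slack beyond the 25%.

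**3. Power if pregnancy losses come on top of the 25%.** The documents give no pregnancy rate, so the shares p below are assumptions. Two cases are shown:

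- No overlap with other attrition: n = 287 × (0.75 − p).
- Pregnancy loss independent of other attrition: n = 287 × 0.75 × (1 − p).

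| Assumed p | n per arm, no overlap | Power | n per arm, independent | Power |
|---|---|---|---|---|
| 5% | 200.9 | 77.2% | 204.5 | 77.9% |
| 10% | 186.6 | 74.1% | 193.7 | 75.7% |
| 15% | 172.2 | 70.7% | 183.0 | 73.3% |

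Power here is Φ(0.27 × √(n/2) − 1.960). An exact t-test calculation gives about 0.2 points less (70.5% in the worst cell). If the 25% already includes pregnancy, about 215 per arm remain and nothing changes.

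**4. Possible bias.** Let p_I and p_C be the shares excluded in the intervention and control arms. Let D be the mean FPG change in excluded women minus that in retained women, taken as equal in both arms. Each retained mean differs from its full-arm mean by −p × D, so the group difference shifts by −(p_I − p_C) × D.

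Again by assumption, take a gap in shares of 5 to 10 points and D of 0.1 to 0.5 mmol/L:

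- Smallest: 0.05 × 0.1 = 0.005 mmol/L, or 0.005 / 0.14 = 4% of the planned difference.
- Largest: 0.10 × 0.5 = 0.05 mmol/L, or 0.05 / 0.14 = 36%.
- Equal shares: zero in this simple model.

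These figures show how the bias would scale. They do not estimate it.

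**The case against.** The strongest defence is that the article never says these women leave the analysis. The criterion stands under participant selection, while the analysis sections promise ITT and add a sensitivity analysis. One could read it to mean that participation ends but the woman's data stay in the mixed model, with the exact analysis set defined in an SAP that is not shown. This stands as a limit on the claim: a reader might infer that the protocol drops such women from the analysis, and the text does not establish that. It does not remove the conflict. The clause is one of eight exclusion criteria, and the only other use of exclusion in the article, for diabetes at baseline, means leaving the study altogether. Two teams could build different primary analysis sets from this text.

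Three further inferences are tempting and are not supported:

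- **That the trial will miss 80% power.** The allowance is for attrition of up to 25% with no list of causes, so it may already cover pregnancy. The lower figures need losses on top of it, and the lowest also needs no overlap with other attrition.
- **That pregnancies will be detected more often in the intervention arm.** More contact makes this possible. But nothing says pregnancy is checked at sessions, calls or the three-month assessment, and both arms attend at 12 months. The plausible gap is mainly pregnancies that begin and end early.
- **That the bias is of a known size.** The documents give neither pregnancy rates by arm nor outcomes in such women.

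The defence is also right that better analysis rules would not restore most of any lost power. A woman pregnant at the 12-month visit has no usable primary value whichever analysis set she is in.

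Finally, there is good reason to treat pregnancy specially, because it directly changes the measured endpoints. That calls for a stated data-handling rule. It does not justify letting an eligibility criterion define the analysis set.

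**Conclusion.** The point holds as a conflict in the text. The during-study part of the pregnancy criterion acts after randomisation and, on its natural reading, removes allocated women. This is incompatible with the two ITT statements and with 12-month follow-up of all recruited women, and nothing shown reconciles them. It is more than missing detail: an SAP that kept these women would depart from the criterion as written.

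The consequence is a possible bias of unknown size, which depends on pregnancy or its detection differing by arm. Power is a side issue. It is unchanged at about 80% if the attrition allowance includes pregnancy. It would be about 70% to 78% if 5 to 15 points of further loss are assumed, and that loss comes largely from pregnancy itself, not from the wording of the criterion.

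**What to change.** Reconcile Selection of participants with Study design, Sample size and power calculation, and Data analysis, so that the during-study clause does not define the analysis set. State that:

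1. Every randomised woman stays in the ITT set in her allocated arm, whether or not she becomes pregnant.
2. FPG, weight and waist values measured during pregnancy are treated as missing in the planned mixed model. All baseline and non-pregnant values are kept, and a sensitivity analysis addresses the assumption made about the missing data.
3. Pregnancies during the 12 months are recorded in the same way in both arms, and counts are reported by arm.
4. The attrition allowance of up to 25% does, or does not, include pregnancy. If it does not, the planned power should be restated with the assumed rate.

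Whether women who become pregnant continue with sessions or tests is a clinical matter. The sponsor should reconcile the passages on it, and no rule is proposed here.

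The cost is a protocol clarification and a little extra missing-data work. The trial is already running, with 134 women randomised by June 4, 2013, so the clarification may need ethics notification, and any woman already removed for pregnancy should be identified and returned to the analysis set with the data she has. The change does not recover 12-month values from women who are pregnant at that visit.
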